## Abstract

**Background:**

Low back pain (LBP) is the first cause of years lived with disability worldwide. This is due to the development of chronic pain. Thus, it is necessary to identify the best therapeutic approaches in the acute phase of LBP to limit the transition to chronic pain. Superficial heat presents the highest level of evidence for short-term reduction in pain and disability in acute LBP. Physical activity is also recommended to avoid transition to chronic LBP, but there is a lack of evidence to determine its effect to reduce acute LBP. Also, the long-term effects of these interventions are unknown. This is a protocol for a randomized controlled trial (RCT) to determine the short and long-term effects of wearable continuous low-level thermal therapy, in combination with exercises or not, on disability and pain.

**Methods/design:**

Sixty-nine participants with acute LBP will be randomly assigned to one of three intervention programs: 1) thermal therapy, 2) thermal therapy + exercises, and 3) control. The interventions will be applied for 7 continuous days. The primary outcome will be disability and secondary outcomes will be pain intensity, pain-related fear, self-efficacy, number of steps walked and perception of change. The evaluators will be blinded to the interventions, and participants will be blinded to other groups’ interventions. Primary and secondary outcomes will be compared between intervention groups.

**Discussion:**

This study will provide new evidence about acute LBP treatments, to limit transition to chronicity. This will be the first study to measure the long-term effects of wearable continuous low-level thermal therapy, combined or not to exercises.

**Trial registration:**

This RCT has been retrospectively registered on ClinicalTrials.gov (NCT03986047) on June 14th, 2019.

## Background

Low back pain (LBP) produces a huge individual and socioeconomic burden through direct and indirect costs, such as patients’ management (imaging, drugs, etc.) and productivity loss, respectively [1, 2]. It is the first cause of years lived with disability in many countries [3]. A study reported that 12 months after LBP onset, pain was still present in 62% of patients [4]. This shows the necessity to find the best treatment approaches in the acute phase in order to prevent the transition from acute to chronic LBP (ALBP/CLBP). The latest clinical guidelines from the “American College of Physicians for ALBP [5]” recommends to select non-pharmacological treatments in the acute phase like superficial heat, massage, vertebral manipulations and acupuncture. The application of superficial heat (“thermal therapy”) presents the strongest evidence (moderate) for short-term reduction in pain [5–8]. Randomized controlled trials (RCT) [9–11] measured the effect of a wearable heatwrap (the most studied form of thermal therapy in ALBP). The results showed that it reduces pain and disability significantly up to 2 days after the end of the intervention in people with acute LBP [9–11]. This effect was superior to ibuprofen, acetaminophen or an oral placebo [11]. Although heatwrap reduces pain in the acute phase of LBP, its long-term effect is unknown. The benefit of this passive treatment may not transfer on the long-term. Active treatment such as exercises and avoiding bed rest could be better suited to influence pain and disability on the long-term. For example, avoiding bed rest is recommended to prevent CLBP [12] and exercises are consistently endorsed by guidelines and systematic reviews to treat CLBP [6, 13]. However, exercises alone have not been shown effective in ALBP [5]. An RCT [9] evaluated the effect of continuous low-level thermal therapy combined with McKenzie exercises during 5 days in LBP patients. The results showed that it reduced pain and disability significantly more than exercises alone, thermal therapy alone or a placebo up to 2 days after the end of the intervention. Thus, the use of heatwrap may provide sufficient pain relief to remain active and better perform exercises, perhaps by reducing fear of movement and increasing self-efficacy. The specific contribution of the present study will be to determine whether the short-term effects of combining thermal therapy and exercises in ALBP transfer to the long-term.

### Objectives and hypothesis

Our principal objective is to determine the effect of wearable continuous low-level thermal therapy combined or not with exercises on disability, pain intensity, pain-related fear, self-efficacy and perception of change in short-term (i) and long-term (ii) in adults presenting ALBP. Our secondary objective is to determine the effect of these interventions on the number of steps walked over the first week of treatment. We hypothesize that the combination of thermal therapy and exercises will have a larger positive effect for all outcomes (disability, pain intensity, pain-related fear, self-efficacy and perception of change) compared to thermal therapy alone and the control group in the short and long-terms. It will also be associated with a higher number of steps walked during the first week of treatment for the group receiving a combination of thermal therapy and exercises suggesting a higher level of physical activity.

## Methods and analysis

### Study setting

The study will take place at the research center (Cirris) in Quebec City, Quebec, Canada.

### Participants

Sixty-nine adults between 18 and 65 years of age presenting ALBP (onset of low back pain with or without leg pain for less than 6 weeks [14]) who have had limited activities or daily routine for more than 1 day will be recruited. The recruitment will be realized through the Quebec Back Pain Consortium’s database, targeted email listings (e.g. Université Laval’s community) and primary care settings by the evaluator. Participants will be included if they score ≥ 10/100 on the Oswestry Disability Index (ODI) questionnaire. This cut-off was chosen to be able to measure a minimal clinically important difference (MCID) of 9 points in ALBP patients [15]). Participants will be excluded if they suffered from LBP in the 3 months preceding the current episode or if they present any sign of specific spinal pathology, like fracture, tumor, spinal infection and obvious signs/symptoms of peripheral and/or central neural impairment (e.g. severe self-reported weakness in lower limb muscles, bilateral reduced sensitivity and/or pins and needles of lower limb skin). They will be excluded if they have a history of lumbar spine surgery, fibromyalgia, rheumatoid arthritis, skin lesion in the lumbar area, alteration of cutaneous sensations or temperature perception, are pregnant or trying to become pregnant, or have cognitive impairments. Also, they will be excluded if they have had a recent change in medication that may influence pain (antidepressant, psychotropic drugs, opioids, etc.), if they had a cortisone infiltration in the last 6 weeks or if they present pain related to pregnancy.

### Study design

A single-blind (evaluator) parallel group RCT will be undertaken. Participants will be randomized to one of three groups: (1) thermal therapy, (2) thermal therapy + exercises, or (3) control; for a 1-week intervention program. Five assessment time points have been established (A_1_ to A_5_ – see Table 1).

**Table 1 Tab1:** Study design

		Study period					
	Enrolment	Baseline	1-week intervention	Post-intervention			
**Time point**	**A**_**0**_	**A**_**1**_	**I**	**A**_**2**_	**A**_**3**_	**A**_**4**_	**A**_**5**_
**ENROLMENT:**							
**Initial screening**	**●**						
**Eligibility assessment**	**●**						
**Informed consent**	**●**						
**Treatment allocation**		**●**					
**INTE****RV****EN****TIONS:**							
**Thermal therapy**			**●**				
**Thermal therapy + exercises**			**●**				
**Control**			**●**				
**ASSE****SS****ME****NTS:**							
**Baseline demographic information**		**●**					
**Physical functioning** (ODI)		**●**		**●**	**●**	**●**	**●**
**Pain** (NRS)		**●**		**●**	**●**	**●**	**●**
**Pain-related fear** (TSK-11)		**●**		**●**	**●**	**●**	**●**
**Self-efficacy** (CDSES −6)		**●**		**●**	**●**	**●**	**●**
**Perception of change** (GRoC)				**●**	**●**	**●**	**●**
**Number of steps walked per day**			**●** (daily)				

A_0_: first contact with participants; A_1_: baseline assessment; I: 7-day intervention; A_2_: assessment 1 week after baseline; A_3_: assessment 4 weeks after baseline; A_4_: assessment 12 weeks after baseline; A_5_: assessment 24 weeks after baseline; ODI: ODI-French Canadian Version; NRS: pain numerical rating scale; TSK: 11-item version of Tampa Scale of Kinesiophobia; CDSES − 6: Chronic Disease Self-Efficacy Scale - Short-Version and GRoC: global rating of change

#### Randomization / blinding

The evaluator will be blinded to the participant’s intervention allocation and participants will be blinded to the nature of the interventions in the other groups. Thus the risks related to the application of heat will be explained only to the participants allocated to thermal therapy groups. The patients will also be unaware of the study objectives and hypotheses. A randomization list will be generated using a computer random number generator by an independent research assistant (allocation concealed in sealed and opaque envelopes) to attribute an intervention program to each participant. Stratification will be done by sex (because men and women may respond differently to interventions in LBP [16]) and ODI score: 1) between 10 and 19 and 2) 20 and more to ensure similar level of disability for each group.

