#### Timeline

First visit: baseline measurements and intervention

*Baseline:* At the baseline assessment, demographic characteristics will be collected before participants complete self-administered questionnaires on symptoms and functional limitations (ODI-French Canadian Version) [15, 17], pain-related fear (11-item version of Tampa Scale of Kinesiophobia – TSK-11) [18] and self-efficacy measured with the Chronic Disease Self-Efficacy Scale - Short-Version (CDSES-6) [19]. Pain intensity will be measured using an 11-point numerical rating scale (NRS) [20, 21] (average previous week [1-week]). These 4 questionnaires will serve as outcome measures (see “Outcome measures” section). The STarT Back Screening Tool [22] and the Canadian minimal dataset for low back pain [23] will be completed to characterise the participants recruited. After baseline assessment*,* participants will be assigned randomly to one of three intervention programs.

*Intervention:* To start, participants will meet a physical therapist (PT) to receive their assigned program (60-min meeting). For participants assigned to the thermal therapy groups (thermal therapy alone and thermal therapy + exercises), a heatwrap (ThermaCare®, Pfizer inc., New York, USA) will be applied onto the lower lumbar spine area, whereas in participants assigned to the control group, a sham non-heat lumbar belt will be applied. In addition, the physical therapist will teach an exercise program to the participants assigned to the “thermal care + exercises” group.
2Intervention program

After the 1st visit, participants will take part in their assigned 7-day intervention program. Every day, participants will indicate in a logbook their average pain level during the day and the adherence to their program. A fitness watch will be given to each participant to record the number of steps walked per day during intervention week. They will be asked to avoid meeting a health care professional for their ALBP during the 7 day-intervention program. After the 7 days, they will be free to do so.
3Second visit – short-term follow-up

A 2nd visit will be realized approximatively 7 days after the 1st visit, and ODI, TSK-11, CDSES-6, average 1-week pain intensity and a global rating of change (GRoC) [24] will be measured to determine the short-term effect of thermal therapy.
4Long-term follow-ups

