### Ethics and dissemination

Ethics approval was obtained from the *Comité d’éthique de la recherche sectoriel en réadaptation et intégration sociale, CIUSSS de la Capitale Nationale* (#2019–1731 – CER CIUSSS-CN) in March 2019. Any modification to the protocol will be submitted to the ethic committee for approval and to clinicaltrials.org. Written informed consent will be obtained from all of the participants, after they read the information brochure describing the project and the potential risks and benefits and after discussing with the investigator if they have any questions. Every participant will be informed that he/she is free to leave the project at any moment. All numeric data collected will be safely stored in files protected with a password, and hard copies will be kept in locked file cabinets. Only study investigators will have access to the data at the completion of the trial. Results of the RCT will be published in a peer-reviewed journal and de-identified data will be available on a public repository at the time of publication. Results will also be communicated through scientific meetings. The International Committee of Medical Journal Editors criteria for authorship will be followed and no professional writer will be involved.

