### Harms

Participants will be asked to write down any minor side effects or adverse events that occurred through the 1-week intervention in the logbook. They will also have a phone number and an e-mail address to reach the PT if they experience any major adverse events or if they have any questions during the week. The PT will then be able to direct the participant to the appropriate resource or give appropriate advices.

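### Only the heat arms are warned of heat risks, yet minor harms rest on each participant's own logbook notes, so harm recording may differ between arms

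*Protocol article*

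**What the plan says.** Under Randomization / blinding, the protocol article states that "participants will be blinded to the nature of the interventions in the other groups" and draws the consequence: "Thus the risks related to the application of heat will be explained only to the participants allocated to thermal therapy groups". It adds: "The patients will also be unaware of the study objectives and hypotheses".

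The order of events is clear. Table 1 marks "Informed consent" at the enrolment contact (A0) and treatment allocation at baseline (A1). The Timeline agrees: "After baseline assessment*,* participants will be assigned randomly to one of three intervention programs".

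The Ethics and dissemination section says that everyone gives written consent "after they read the information brochure describing the project and the potential risks and benefits". It makes no exception for heat.

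On harms, the plan is: "Participants will be asked to write down any minor side effects or adverse events that occurred through the 1-week intervention in the logbook". For major events, participants are given a telephone number and an e-mail address to reach the physical therapist. The Intervention programs section has the control arm wear a wrap at room temperature for eight hours a day over the same seven days as the heat arms.

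**The concern.** For minor harms the participant is the assessor. What a participant has been told beforehand can affect what is noticed, what is attributed to the wrap and what is thought worth writing down. The plan gives two arms a warning about heat and gives the third none. Yet local effects of wearing something on the lower back all day, such as skin irritation, could occur in any arm, and the sham is there to control for the wrap itself. If minor events are later tabulated by arm, an excess under heat could reflect the heat, the warning or both, and the data could not separate them.

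A second, smaller matter is how the sections fit together. A reader cannot tell whether the brochure read before consent mentions heat risks. If it does, the statement that only the heat arms are told is not accurate, and controls could learn what the other arms receive. If it does not, the Ethics section's account of consent is incomplete for participants later assigned to heat.

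**Working it through.** **Inputs from the protocol article**
- Group size: 23 per arm and 69 in total (Sample size & statistical analysis). Heat arms: 2 × 23 = 46. Sham arm: 23.
- Harm rates, reporting probabilities and a harms analysis: none given. There is thus no figure of the plan's own on this point to reproduce.

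**Sequence, with the sections set side by side**
1. Enrolment (A0): consent after the brochure, for everyone (Table 1; Ethics and dissemination).
2. Baseline (A1): assessment, then random allocation (Table 1; Timeline).
3. After allocation: heat risks explained to the 46 heat participants and not to the 23 controls (Randomization / blinding).
4. Intervention week: all 69 are asked to record minor events in their own logbook (Harms).

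Step 3 comes before step 4 and differs by arm. Step 4 as described is the same in every arm, but it relies on the judgement of people who were informed differently at step 3. The Harms section describes no evaluator questioning and no blinded harm assessment that would offset this.

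**Illustration of size (all rates assumed)**
Let p be the true rate of a minor effect, equal in all arms. Let r_w be the probability that a warned participant records it, and r_u the same for an unwarned participant.
- Recorded rate, heat = p × r_w; recorded rate, sham = p × r_u.
- Apparent risk ratio = (p × r_w) / (p × r_u) = r_w / r_u, which does not depend on p.

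| r_w | r_u | Apparent risk ratio | Expected reports at p = 20%: heat (46) | Sham (23) |
|---|---|---|---|---|
| 0.9 | 0.9 | 1.00 | 46 × 0.20 × 0.9 = 8.3 | 23 × 0.20 × 0.9 = 4.1 |
| 0.8 | 0.6 | 0.8/0.6 = 1.33 | 46 × 0.20 × 0.8 = 7.4 | 23 × 0.20 × 0.6 = 2.8 |
| 0.9 | 0.5 | 0.9/0.5 = 1.80 | 46 × 0.20 × 0.9 = 8.3 | 23 × 0.20 × 0.5 = 2.3 |

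The ratios are the same at p = 10% or 30%; only the counts change. The direction is plausible, but nothing in the documents favours one row over another.

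**The case against.** The strongest reply is that the selective disclosure is a declared part of participant blinding, in a study with ethics approval, and that it protects the comparisons that matter. The primary outcome (ODI) and nearly all secondary outcomes are self-reported, so keeping controls unaware of heat in the other arms has real value. This stands. It rules out one tempting remedy, which is to tell everyone that the wrap may or may not be warm. A participant wearing a room-temperature wrap would recognise the sham at once.

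It can also be said that the plan lists no harm outcome and no between-arm test of harms, that all arms receive the same request and the same contact route, and that the logbook's layout is not shown. These points stand too. The notes are requested, not unprompted, and the article does not say that heat participants are told of particular skin effects. But an identical request does not remove a difference created by what was said before it.

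A reader might infer three stronger things that the documents do not support:
- **That the consent passage is contradicted.** The Ethics section does not say that the brochure lists heat risks, and the brochure is not shown. A general brochure followed by arm-specific explanation is compatible with both statements. What remains is an unexplained fit between sections.
- **That harm rates are not comparable.** This would need evidence that warned and unwarned participants actually record differently. The documents give none.
- **That the warning will cause withdrawals from the heat arms only.** One withdrawal is 1/23 = 4.3% of an arm, but nothing suggests that anyone would leave on hearing the risks. The sample size already allows for 10% loss, or 0.10 × 23 = 2.3 per arm.

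**Conclusion.** The point holds as a risk of differential ascertainment. By design, 46 participants record minor harms after a warning and 23 without one. The size of the effect cannot be derived from the documents; the range of 1.00 to 1.80 above rests wholly on assumed reporting probabilities. The conclusion assumes that at least some minor effects, such as irritation under the wrap, can occur in any arm, and that minor events will at some stage be described by arm. It does not touch the primary or secondary efficacy analyses.

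Separately, Randomization / blinding, Table 1 and Ethics and dissemination need to be reconciled, as a matter of clarity. This is a cheap improvement and not a flaw that undermines the trial.

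**What to change.** 1. **Logbook.** Put the same short structured checklist in every arm's logbook: skin redness, itching or irritation under the wrap or belt, increased pain, and other, each rated none, mild or more. Word it neutrally so that it fits any wrap or belt, and do not mention heat. This keeps the masking and gives every participant the same cue at the time of recording. It should narrow the reporting gap but cannot be assumed to close it.
2. **Reporting.** When harms are presented by arm, state as a limitation that only the heat arms were told of heat risks.
3. **Text.** Reconcile the three sections by stating which risks the pre-consent brochure covers and, if that is the approved procedure, that arm-specific heat risks are explained after allocation.

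Do not disclose the warm versus unheated contrast to all participants, since that would give up masking for self-reported outcomes.

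Cost: an ethics amendment, slightly more logbook burden, and possibly more minor events recorded in all arms. The article describes the registration as retrospective, so recruitment may already have begun. If so, note which logbook version each participant used.

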#### Timeline

First visit: baseline measurements and intervention

*Baseline:* At the baseline assessment, demographic characteristics will be collected before participants complete self-administered questionnaires on symptoms and functional limitations (ODI-French Canadian Version) [15, 17], pain-related fear (11-item version of Tampa Scale of Kinesiophobia – TSK-11) [18] and self-efficacy measured with the Chronic Disease Self-Efficacy Scale - Short-Version (CDSES-6) [19]. Pain intensity will be measured using an 11-point numerical rating scale (NRS) [20, 21] (average previous week [1-week]). These 4 questionnaires will serve as outcome measures (see “Outcome measures” section). The STarT Back Screening Tool [22] and the Canadian minimal dataset for low back pain [23] will be completed to characterise the participants recruited. After baseline assessment*,* participants will be assigned randomly to one of three intervention programs.

*Intervention:* To start, participants will meet a physical therapist (PT) to receive their assigned program (60-min meeting). For participants assigned to the thermal therapy groups (thermal therapy alone and thermal therapy + exercises), a heatwrap (ThermaCare®, Pfizer inc., New York, USA) will be applied onto the lower lumbar spine area, whereas in participants assigned to the control group, a sham non-heat lumbar belt will be applied. In addition, the physical therapist will teach an exercise program to the participants assigned to the “thermal care + exercises” group.
2Intervention program

After the 1st visit, participants will take part in their assigned 7-day intervention program. Every day, participants will indicate in a logbook their average pain level during the day and the adherence to their program. A fitness watch will be given to each participant to record the number of steps walked per day during intervention week. They will be asked to avoid meeting a health care professional for their ALBP during the 7 day-intervention program. After the 7 days, they will be free to do so.
3Second visit – short-term follow-up

A 2nd visit will be realized approximatively 7 days after the 1st visit, and ODI, TSK-11, CDSES-6, average 1-week pain intensity and a global rating of change (GRoC) [24] will be measured to determine the short-term effect of thermal therapy.
4Long-term follow-ups

At 4, 12 and 24 weeks after baseline assessment, the average 1-week pain intensity, TSK-11, ODI, CDSES-6 and GRoC will be completed electronically by each participant. Participants will also report the use of other interventions after the completion of the 7-day intervention (e.g. medication, psychological support, health care professional, exercises training).

